### Sample size and power calculations

Assuming no interactions between the two main effects as discussed earlier, the target sample size will be 240 participants (120 participants in the GLC group and 120 participants on oral medication). This is based on: a power calculation using a 5% significance level, 80% power comparing two proportions, and current knowledge of the average ovulation rates of lifestyle interventions and letrozole, our primary comparison. We explored a number of combinations of the ovulation rates from letrozole and lifestyle interventions and chose the most conservative estimate to ensure that our sample size was adequate, i.e., 91 in each group. By enrolling 120 participants in each group, we have allowed for a drop-out rate of 32%. Table 1 describes the lowest and highest reported ovulation rates for letrozole and lifestyle interventions, the sample size required in each scenario comparing the two proportions, and the three highest sample sizes required from our calculations, accounting for the length of lifestyle intervention and the start dose of letrozole.

**Table 1 Tab1:** Sample size calculation based on previous literature

Range of reported ovulation rates	Letrozole ovulation rate	Lifestyle ovulation rate	Total sample size needed
Lowest	62%^a^	38%^b^	130
Highest	86%^c^	67%^d^	150
Median	70%	50%	182

^a^Legro et al. [29]

^b^Palomba et al. [36]

^c^Zeinalzadeh et al. [37]

^d^Karimzadeh and Javedani [38]

When calculating the sample size necessary to assess the effect of myo-inositol on ovulation rates, we reviewed the few published studies available acknowledging that these studies all had small sample size. One randomized controlled trial reported an ovulation rate of 70% when myo-inositol was given to women with PCOS versus a 21% ovulation rate in controls [24]. Similarly, another randomized controlled trial reported an ovulation rate of 65% using myo-inositol in PCOS [32]. Using these rates in a comparison of two proportions, a total sample size of 26 is needed, and easily covered by our original calculation above.

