## Methods/design

### Overall study design

Women diagnosed with PCOS will be recruited at the Grace Fertility and Reproductive Medicine Centre in Vancouver, Canada. This study follows a factorial design (Fig. 1). Participants will be randomized with a 1:1 allocation into two groups: the first group participating in a comprehensive lifestyle intervention program provided by our clinic (“Graceful Lifestyle Changes” (GLC) program) while the second group will be prescribed letrozole to induce ovulation, with the standard physician counseling (Fig. 2). Within each group, participants will be further randomized with a 1:1 allocation to either receive oral myo-inositol or a placebo. Block randomization will be performed at both stages using a computer-generated random numbers table and the software program REDCap. All clinicians, research scientists and participants involved in the study will be blinded to block sizes and allocation of myo-inositol/placebo. A researcher not involved in the study will be responsible for the randomization procedures. A data monitoring committee will not be necessary given the known safety of the proposed interventions. The SPIRIT 2013 Checklist for trial protocols has been included (see Additional file 1).

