## Statistical methods

The participants’ biochemical and hormonal profiles, physical attributes (body mass index (BMI), hirsutism), ovulatory response, pregnancy status, scores for depression, anxiety, stress and quality of life will be assessed for statistical normality. Each main effect will be compared by analysis of variance (ANOVA) or its non-parametric equivalents. The primary comparison will be between GLC and letrozole. The observed effects of myo-inositol alone are small in clinical experience and there are no reported interactions between myo-inositol and ovulation-induction medications or lifestyle change in the literature. Hence, our power calculations (see below) have been based on the two main effects acting independently. However, our factorial design will provide an opportunity to explore potential interactions (acknowledging the sample size required would change in the presence of interactions) [30, 31]. Categorical data will be compared by chi-square statistics. Differences in dietary intake and dietary composition over time will be compared by ANOVA or its non-parametric equivalent with time as the repetitive measure. Regression analysis will also be performed to determine the individual impacts of diet, activity, and mindfulness on ovulation. In addition, membership in the four PCOS sub-groups will be further explored as a potential predictor for ovulation rates in regression analysis after adjusting for BMI and age.

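### The primary comparison and the myo-inositol comparison are sized on incompatible myo-inositol effects, so the stated 80% power for GLC versus letrozole depends on which effect is true

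*Protocol article*

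**What the plan says.** Under Overall study design, women are randomized to GLC or letrozole, and then: "Within each group, participants will be further randomized with a 1:1 allocation to either receive oral myo-inositol or a placebo". Half of each arm in the primary comparison therefore takes active myo-inositol.

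The Statistical methods section names GLC versus letrozole as the primary comparison. It says that myo-inositol on its own has shown only small effects in clinical experience and that no interactions have been reported. From this it concludes that "our power calculations (see below) have been based on the two main effects acting independently". It adds that the required sample size would change if interactions were present.

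The Sample size section uses "a power calculation using a 5% significance level, 80% power comparing two proportions" and bases the rates on "current knowledge of the average ovulation rates of lifestyle interventions and letrozole, our primary comparison". The Table 1 row that sets the size is "Median 70% 50% 182"; the authors say that they "chose the most conservative estimate to ensure that our sample size was adequate, i.e., 91 in each group". They enrol 120 per group.

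The same section then sizes myo-inositol from published trials that it acknowledges were small. One "reported an ovulation rate of 70% when myo-inositol was given to women with PCOS versus a 21% ovulation rate in controls"; another gave 65% on myo-inositol. The resulting total is 26, described as easily covered.

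**The concern.** The groups actually compared are 50:50 mixtures of women with and without myo-inositol, so their expected ovulation rates are not 70% and 50% unless myo-inositol does nothing. Leaving it out does no harm if the effect is small, or if it adds the same number of points to both arms.

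The effect used to size the second factor is 49 points. Added to the letrozole rate it gives 70 + 49 = 119%, and added to the lifestyle rate 50 + 49 = 99%. With the 65% rate (44 points) the sums are 114% and 94%. On the proportion scale of the sample-size calculation, these inputs and the absence of interaction cannot all hold: letrozole reaches the ceiling first and the gap narrows.

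So one of the two calculations is unsupported. At stake is either the power of the primary comparison or the claim that the myo-inositol question is easily covered.

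**Working it through.** **Inputs from the protocol.** 5% level and 80% power; 70% versus 50%; 91 evaluable and 120 enrolled per group; 1:1 myo-inositol allocation within arms; myo-inositol 70% (or 65%) versus 21%.

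**Assumptions.** Two-sided test (this reproduces the stated sizes). The 70% and 50% rates apply to the placebo halves. The 65% rate is set against the same 21%. The scale on which the effects combine is not given, so three are tried.

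**Reproducing the plan.** n per group = (1.960 + 0.842)² × [p₁(1−p₁) + p₂(1−p₂)] / (p₁−p₂)².
- 70% vs 50%: 7.849 × 0.46 / 0.04 = 90.3, so 91 per group and 182 in total. The other Table 1 rows give 130 and 150. All three match.
- 70% vs 21%: 7.849 × 0.3759 / 0.2401 = 12.3, so 26 in total. This matches. The 65% rate would give 32.

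**Power at the mixed rates.** Each arm's rate is the mean of its placebo half and its myo-inositol half. Power = Φ(|p₁−p₂| / √{[p₁(1−p₁) + p₂(1−p₂)]/n} − 1.96). With no myo-inositol effect it is 80% at 91 and 90% at 120.

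*Large effect.* The odds ratio is (0.70/0.30)/(0.21/0.79) = 8.8, or 7.0 with 65%. The ratio of non-ovulation is 0.30/0.79 = 0.38, or 0.44 with 65%.

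| Myo-inositol rate (vs 21%) | Scale | Letrozole arm | GLC arm | Gap (points) | Power, 91 | Power, 120 |
|---|---|---|---|---|---|---|
| 70% | constant odds ratio | 82.7% | 69.9% | 12.8 | 54% | 65% |
| 70% | constant cut in non-ovulation | 79.3% | 65.5% | 13.8 | 56% | 68% |
| 70% | +49 points, capped at 100% | 85.0% | 74.5% | 10.5 | 43% | 53% |
| 65% | constant odds ratio | 82.1% | 68.7% | 13.4 | 56% | 68% |
| 65% | constant cut in non-ovulation | 78.4% | 63.9% | 14.4 | 59% | 70% |
| 65% | +44 points, capped at 100% | 85.0% | 72.0% | 13.0 | 58% | 70% |

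First row in full: an odds ratio of 8.8 takes 70% to 95.3% and 50% to 89.8%, and the means are (70 + 95.3)/2 = 82.7% and (50 + 89.8)/2 = 69.9%. For 80% power these cases need 302 to 454 evaluable women in total, against 182.

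*Small effect (assumed odds ratios).*

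| Odds ratio | Letrozole arm | GLC arm | Gap (points) | Power, 91 | Power, 120 |
|---|---|---|---|---|---|
| 1.25 | 72.2% | 52.8% | 19.5 | 79% | 89% |
| 1.5 | 73.9% | 55.0% | 18.9 | 77% | 88% |
| 2 | 76.2% | 58.3% | 17.8 | 74% | 85% |

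*Feasible additive effect.* Adding 10 to 30 points to both arms keeps the gap at 20 points, and power at 91 per group rises to 82% to 89%.

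**The other side of the conflict.** If the effect is small, check the total of 26. As an illustration, take 60% on placebo (the mean of 70% and 50%) and 70% on myo-inositol, an odds ratio of (0.70/0.30)/(0.60/0.40) = 1.56. Power at 91 per myo-inositol group is about 30%. Reaching 80% would take 7.849 × (0.24 + 0.21)/0.01 = 353.2, so 354 per group.

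**The case against.** The strongest reply is that the protocol gives a premise for leaving myo-inositol out: a small effect and no reported interaction. Under that premise the primary power is little affected. It falls by 1 to 6 points at 91 per group for odds ratios from 1.25 to 2, and stays at 85% or more if all 120 are evaluable. The authors also acknowledge that interactions would change the sample size, and they flag that the myo-inositol trials were small. All of this stands, and it is why the power loss can only be stated conditionally.

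A reader might go further and infer that the primary power simply is about 43% to 56%. The documents do not support that. The protocol has no single myo-inositol effect, and the scales above are assumptions. The 43% comes from truncating an impossible 119% at 100%. The range also applies only to the 70%/50% row with the full loss to 91. The other Table 1 rows, under the same large effects at 91 per group, give about 52% to 71% (86%/67%) and 67% to 89% (62%/38%).

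A reader might also infer that a non-significant result is meant to show that GLC matches letrozole. The protocol states no equivalence or non-inferiority aim.

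It can also be said that the planned analysis of variance could adjust for myo-inositol. Approximate stratified calculations for the six large-effect cases give 53% to 67% at 91 per group, so adjustment recovers part of the loss but not 80%.

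None of this reconciles the small effect in one section with the 49-point effect in the next.

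**Conclusion.** The firm finding is the contradiction. One section relies on a small myo-inositol effect to protect the primary sample size; the next relies on a very large one to declare the myo-inositol question covered.

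- **Small effect (assumed odds ratio 1.25 to 2):** the primary power nearly stands, but the total of 26 has no basis.
- **Effect as large as cited:** the 26 stands for the 70% rate, but the primary gap falls to about 10 to 14 points. Power is then below 80% on every scale tried for the 70%/50% row, even without drop-out.
- **Feasible additive effect:** primary power is not reduced, but the 49-point effect used for the 26 is not feasible at the planned rates.

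The stated 80% is therefore a conditional figure. This is worth correcting before recruitment, which the Trial status section says had not begun. It does not show that the trial is underpowered as a matter of fact.

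**What to change.** In Statistical methods and in Sample size and power calculations:

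1. State one myo-inositol effect and the scale on which no interaction is assumed (for example, the odds ratio), and use both in the two calculations.
2. Restate the primary power at the resulting pooled arm rates, as conditional. For example: with 91 per group, about 77% if the myo-inositol odds ratio is 1.5, 74% if it is 2, and about 54% if it is 8.8, as the cited 70% versus 21% implies.
3. Replace the total of 26, or qualify it, so that it matches the effect chosen.
4. State that the GLC–letrozole difference will be reported within the placebo and myo-inositol strata beside the pooled result, so that a narrowed pooled gap can be recognised.

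The cost is some rewording and one extra table from data already collected. The stated power becomes less favourable if the chosen effect narrows the gap, and the stratum estimates, with 60 enrolled per cell, will be imprecise. Enrolment and treatment do not change.

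### The 91 per group is correct for the median rates (70% vs 50%), but Table 1's own rates do not support calling it the most conservative choice: 62% vs 50% would need 530 in total, not 182

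*Protocol article*

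**What the plan says.** The trial compares the lifestyle programme (GLC) with letrozole: "The primary comparison will be between GLC and letrozole". Under Sample size and power calculations, the size rests on "a power calculation using a 5% significance level, 80% power comparing two proportions" and on what is known of average ovulation rates. The authors report trying a number of rate combinations, and state that they "chose the most conservative estimate to ensure that our sample size was adequate, i.e., 91 in each group". Enrolment is set at 120 per group to allow for drop-out.

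The same section says that Table 1 gives the lowest and highest reported rates, with the size needed in each scenario, and "the three highest sample sizes required from our calculations". A qualifier follows: the calculations took account of how long the lifestyle intervention lasted and of the letrozole starting dose. Table 1 has three rows:

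| Row | Letrozole | Lifestyle | Total N |
|---|---|---|---|
| Lowest | 62% | 38% | 130 |
| Highest | 86% | 67% | 150 |
| Median | 70% | 50% | 182 |

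**The concern.** The sample size for two proportions depends mainly on the difference between them. Each row of Table 1 takes both rates from the same position in their ranges, so the three differences are 24, 19 and 20 points. The four extreme rates are footnoted to four different studies, and the text gives no reason why a low letrozole rate should go with a low lifestyle rate. A conservative choice over a range of reported rates would also consider pairs in which the two rates lie closer together, and none is shown.

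What is at stake is how a result will be read. If readers believe the size is conservative over the reported rates, they may take a non-significant difference as evidence that GLC matches letrozole, when the trial may have had little power for the true difference.

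**Working it through.** **Inputs.** Significance level 5% and power 80% (Sample size and power calculations); 1:1 allocation (Overall study design); rates from Table 1. The article does not say whether the test is one- or two-sided. Two-sided reproduces the table; one-sided, with a pooled null variance, gives 106, 122 and 148.

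**Formula.** With p1 for letrozole and p2 for lifestyle, and unpooled variance:

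n per group = (1.96 + 0.8416)² × [p1(1−p1) + p2(1−p2)] / (p1−p2)², where (1.96 + 0.8416)² = 7.849, rounded up.

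**Reproducing Table 1.**
- 62% vs 38%: 7.849 × 0.4712 / 0.0576 = 64.2, so 65 per group, total 130.
- 86% vs 67%: 7.849 × 0.3415 / 0.0361 = 74.3, so 75 per group, total 150.
- 70% vs 50%: 7.849 × 0.4600 / 0.0400 = 90.3, so 91 per group, total 182.

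All three match exactly. A pooled null variance gives 134, 154 and 186.

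**The six pairs not shown, by the same formula.**

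| Letrozole vs lifestyle | Difference (points) | n per group | Total N |
|---|---|---|---|
| 86% vs 38% | 48 | 13 | 26 |
| 86% vs 50% | 36 | 23 | 46 |
| 70% vs 38% | 32 | 35 | 70 |
| 62% vs 50% | 12 | 265 | 530 |
| 62% vs 67% | −5 | 1,434 | 2,868 |
| 70% vs 67% | 3 | 3,760 | 7,520 |

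Three need fewer than 182 and three need more. For 62% vs 50%: 7.849 × 0.4856 / 0.0144 = 264.7, so 265 per group. That total of 530 is 2.9 times 182 (530/182).

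**Power at the trial's size.** Normal approximation with pooled variance under the null: power = Φ[(|p1−p2| − 1.96 × SE0) / SE1], where SE0² = 2p̄(1−p̄)/n, SE1² = [p1(1−p1) + p2(1−p2)]/n and p̄ is the mean of the two rates.

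For 62% vs 50%, p̄ = 0.56:
- n = 91: SE0 = √(0.4928/91) = 0.0736 and SE1 = √(0.4856/91) = 0.0730. (0.12 − 0.1442)/0.0730 = −0.33, so power is 37%.
- n = 120: SE0 = 0.0641 and SE1 = 0.0636. (0.12 − 0.1256)/0.0636 = −0.09, so power is 46%.

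| Pair | Power, 91 per group | Power, 120 per group |
|---|---|---|
| 62% vs 38% | 91% | 96% |
| 86% vs 67% | 86% | 94% |
| 70% vs 50% | 79% | 89% |
| 62% vs 50% | 37% | 46% |
| 62% vs 67% | 10% | 12% |
| 70% vs 67% | 6% | 7% |

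The 79% for the median pair, against the planned 80%, only reflects the pooled null variance used for power here; the article's formula leaves the variance unpooled.

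**The case against.** The strongest reply is the qualifier on intervention length and letrozole starting dose. It suggests that the authors worked with a restricted set of combinations, drawn from cited studies that are not at hand, and that 182 may be the largest total within that set. A condensed article need not list every combination tried, so it cannot be shown that only three were. This stands in part. But the qualifier names no excluded pair, and Table 1 presents its rates as the range of reported rates. A reader of the article therefore has no ground for setting 62% vs 50% aside.

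The second reply is that planning on central estimates is ordinary practice, and that the section itself cites average rates. This stands in full as a defence of the number 91. It does not defend the description, because a size based on median rates is a central assumption and not a conservative one.

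The third reply is that the two most extreme pairs prove little. A 3-point difference is no sensible target, and crossing the lowest rate of one arm with the highest of the other makes almost any sizing look inadequate. This is fair. The point needs only 62% vs 50%.

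Finally, rates, significance level, power and size are all disclosed, so a careful reader can see which difference the trial is built for. That limits the harm but does not make the description accurate.

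**Conclusion.** The calculation is right and the claim about it is not. For the median rates, 91 per group is correct. It is the largest of the three rows shown, but not the largest over the rates in the table: 62% vs 50% needs 530 in total, and the trial's power for that pair is about 37% (91 per group) to 46% (120 per group). The statement that the table holds the three highest sizes fails for the same reason, unless an exclusion applied that the article does not state.

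A reader might infer three stronger things, and the document supports none of them:
- That there is a sample-size error, or that the trial must be enlarged. Sizing for a 20-point difference is a legitimate choice, and the arithmetic reproduces.
- That the unshown pairs generally need more. Half of them need only 26 to 70.
- That adequate power exists only at a difference of 20 points. It exists for differences of about 20 points or more, and the exact threshold shifts with the rates: 86% vs 67%, at 19 points, has about 86% with 91 per group.

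The conclusion assumes a two-sided test and the unpooled formula, both inferred from the exact match with Table 1. A pooled null variance gives 536 instead of 530 for 62% vs 50%, which changes nothing.

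**What to change.** In Sample size and power calculations, remove the description of 91 per group as the most conservative estimate and the statement that Table 1 holds the three highest sizes. Replace them with wording such as: *The trial is sized for the median reported rates, 70% with letrozole and 50% with lifestyle intervention. With 91 evaluable participants per group, power is about 80% for a difference of about 20 points or more (about 89% for 70% vs 50% if all 120 are evaluable). Power is lower for smaller differences, for example about 37% (46%) for 62% vs 50%.*

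If intervention length or starting dose did rule out certain combinations, say which ones and why.

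The cost is a few sentences. Enrolment, design and analysis stay as they are, and the trial had not begun recruiting when the article was written. The stated property becomes less favourable, but it is then one that the table supports.

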### Potential biases or limitations

The drop-out rate is often high in lifestyle-based interventions. To mitigate a high drop-out rate we have taken steps such as providing daily email contacts and weekly check-ins between participants and health care providers throughout the duration of the study (12 weeks). A lack of compliance can often become another limitation for intervention studies. To ensure compliance of participants, especially with the lifestyle modification group, we will provide weekly in-person education sessions, as well as periodic check-ins over the phone, in order to explain and reinforce the importance and significance of the recommendations provided and how our study participants might directly benefit from such comprehensive lifestyle changes. These weekly sessions will provide an opportunity for participants to ask questions and receive support from both clinicians and other women struggling with similar issues. After each session, the participant’s weight will be recorded (in a private setting) to help them remain motivated in adhering to the dietary changes and increased physical activity. Several dietary recall methods will be used to measure compliance to the low-glycemic diet, such as a 24-h recall and a food frequency questionnaire, recognizing these tools also have their own limitations.

Although the main goal of this intervention is to achieve a pregnancy, improving overall health and quality of life for women with PCOS is an important component in achieving this primary goal. Infertility per se has a significant psychological impact on women, as does the diagnosis of PCOS. Failed repetitive cycles of hormone therapy further adds to stress and reduced quality of life in PCOS, providing a rationale to develop a comprehensive support program for sustainable lifestyle changes. In addition to improving ovulatory function and the chance of conceiving, such a program has the potential to enhance long-term physical and mental health in this population.

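### Enrolling 120 per group to keep 91 allows for 24% drop-out, not the stated 32%; at 32% the trial falls short of 80% power in its own sizing scenario

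*Protocol article*

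**What the plan says.** The protocol article, under Sample size and power calculations, bases the trial size on "a power calculation using a 5% significance level, 80% power comparing two proportions". Table 1 gives three scenarios, and the largest requirement is the row "Median 70% 50% 182" (letrozole rate, lifestyle rate, total sample size). The authors say they "chose the most conservative estimate to ensure that our sample size was adequate, i.e., 91 in each group".

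They then set enrolment: "the target sample size will be 240 participants (120 participants in the GLC group and 120 participants on oral medication". The drop-out allowance follows from these two numbers: "By enrolling 120 participants in each group, we have allowed for a drop-out rate of 32" per cent.

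Under Potential biases or limitations the article adds: "The drop-out rate is often high in lifestyle-based interventions".

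**The concern.** A drop-out rate is the share of enrolled participants who are lost, so its denominator is the number enrolled. With 120 enrolled and 91 needed, the stated 32% looks as if it was taken over 91. If so, the sentence overstates the protection that the trial has against attrition and contradicts the requirement of 91 given just before it.

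The primary comparison (lifestyle programme versus letrozole) is at stake. The article itself names attrition as a risk of this kind of intervention, and 32% is the only tolerance for it that the article states. Anyone reading the plan would take a loss of, say, 28% in each group as covered, although fewer than 91 women per group would remain.

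**Working it through.** **Inputs** (all from Sample size and power calculations, except the 1:1 allocation, which is from Overall study design)

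- Significance level 5%, power 80%. The number of sides is not stated; two-sided reproduces the table.
- Sizing scenario: letrozole 70%, lifestyle 50%.
- Required: 91 per group (182 in total). Enrolled: 120 per group (240 in total).
- Stated drop-out allowance: 32%.

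**Step 1. Reproduce the base size.** With the unpooled normal approximation, n per group = (1.960 + 0.842)² × [p₁(1−p₁) + p₂(1−p₂)] / (p₁−p₂)², where (1.960 + 0.842)² ≈ 7.849.

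| Scenario | Calculation | n per group | Total | Table 1 |
|---|---|---|---|---|
| 62% vs 38% | 7.849 × 0.4712 / 0.0576 = 64.2 | 65 | 130 | 130 |
| 86% vs 67% | 7.849 × 0.3415 / 0.0361 = 74.2 | 75 | 150 | 150 |
| 70% vs 50% | 7.849 × 0.4600 / 0.0400 = 90.3 | 91 | 182 | 182 |

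All three rows match, so the base requirement of 91 is sound by the protocol's own method. It has almost no slack: power at 91 per group is 80.3%.

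**Step 2. Check the drop-out allowance.**

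- As a share of those enrolled: (120 − 91)/120 = 29/120 = 24.2%.
- As inflation over the number required: (120 − 91)/91 = 29/91 = 31.9%.

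Only the second gives 32%. The protocol has in effect used n × (1 + d), 91 × 1.32 = 120.1, where n/(1 − d) is needed. With the correct form, d = 24% gives 91/0.76 = 119.7, so 120 per group; d = 32% gives 91/0.68 = 133.8, so 134 per group, or 268 in total.

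**Step 3. What remains at 32% drop-out.** 120 × 0.68 = 81.6, that is 81 or 82 women per group, and 91 − 81.6 = 9.4 short of the requirement.

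**Step 4. Power at that size, 70% versus 50%, two-sided 5%.**

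- Unpooled (the form that reproduces Table 1): Φ(0.20/√(0.46/n) − 1.960).
- Pooled null variance (the form that corresponds to the usual chi-square test): Φ((0.20√n − 1.960√0.48)/√0.46).

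| n per group | Unpooled | Pooled |
|---|---|---|
| 91 | 80.3% | 79.1% |
| 82 | 76.1% | 74.8% |
| 81 | 75.6% | 74.3% |

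Within either formula, the loss from 91 to 82 per group is a little over 4 percentage points. The risk of missing the target difference rises from about 20% to about 24–26%.

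**The case against.** The arithmetic has no real defence: the text says drop-out rate, and no reading of that term leaves 91 women after 32% of 120 are lost. The case on the other side concerns how much it matters.

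- **Formula.** Setting a pooled 75% against a nominal 80% adds about one point that comes from the formula and not from drop-out, because the pooled form gives only 79.1% at 91 per group. This is fair. Like for like, the loss is about 4 points, and 76% is the figure that matches Table 1. The pooled value is still relevant because the article plans chi-square tests for categorical data. Both are below 80%.
- **Other scenarios.** At 81–82 per group, power is about 82% pooled (83–84% unpooled) for 86% versus 67%, and about 87% pooled (88–89% unpooled) for 62% versus 38%. This stands. The shortfall is confined to the 70% versus 50% row, but that is the row on which the protocol chose to size the trial.
- **Loss in one group only.** The article's remark on attrition concerns lifestyle interventions. If the lifestyle group fell to 82 and the letrozole group lost 10% (an assumption; 108 left), unpooled power would be 80.8%; with 15% lost (102 left), 79.9%. This also stands: the power loss computed above needs a similar loss in both groups. The allowance, however, is stated for each group.
- **Practical effect.** The article ties no monitoring rule to the 32%, and correcting the figure restores no power. Both are true. The sentence nevertheless makes a claim about the adequacy of the trial size that its own numbers contradict.

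**Conclusion.** The concern holds. Enrolling 120 per group to retain 91 tolerates at most 24.2% drop-out; the stated 32% overstates this by about 8 percentage points. At 32% drop-out in each group, 81–82 women per group remain, and power for 70% versus 50% is about 74–76%, depending on the variance form, not 80%.

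The conclusion on the allowance rests only on the protocol's 91 and 120. The power figures also assume a two-sided 5% test, equal loss in the two groups, and that women who drop out provide no primary outcome, as the protocol's own inflation for drop-out implies. The base size of 91 per group is not in question.

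**What to change.** Replace 32% with 24% in the drop-out sentence. Add that if 32% of each group dropped out, about 82 women per group would be evaluable and power for 70% versus 50% would be about 75% (76% by the formula behind Table 1). This costs one corrected sentence and no extra participants; the stated allowance becomes less favourable.

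If the sponsor wants a true 32% allowance with 91 retained, enrolment has to rise to 134 per group, 268 in total, which is 28 more women than planned. The article's Trial status section says recruitment had not begun, so at that point either correction was open.

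### The myo-inositol sample size of 26 uses a 21% control rate that does not fit a trial in which every placebo woman also receives lifestyle intervention or letrozole; the detectable gain is about 17–19 points at a 60% placebo rate

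*Protocol article*

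**What the plan says.** All references are to the protocol article.

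- **Overall study design.** Women are first allocated to the lifestyle programme (GLC) or letrozole. Then: "Within each group, participants will be further randomized with a 1:1 allocation to either receive oral myo-inositol or a placebo". No cell is left without a background treatment.
- **Sample size and power calculations.** The general basis is "a power calculation using a 5% significance level, 80% power comparing two proportions". For myo-inositol, the section cites one trial with "an ovulation rate of 70% when myo-inositol was given to women with PCOS versus a 21% ovulation rate in controls", adds that "another randomized controlled trial reported an ovulation rate of 65% using myo-inositol in PCOS", and concludes that "a total sample size of 26 is needed, and easily covered by our original calculation above". It acknowledges that the published studies were small.
- **Table 1, same section.** Ovulation rates for letrozole and lifestyle are 62% and 38% (lowest), 86% and 67% (highest), and 70% and 50% (median). The median row gives the 91 per group behind the target of 240.
- **Statistical methods.** "The observed effects of myo-inositol alone are small in clinical experience". The power calculations treat the two main effects as independent.
- **Background, objectives.** Whether adding myo-inositol improves ovulation rates is a stated objective.

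**The concern.** The size of a comparison depends on the rate expected in its control group. Here that group is the placebo half of the trial: women on GLC or letrozole plus placebo. The calculation instead takes 21% from another trial's controls. That is well below the lowest rate Table 1 gives for either background treatment (38%). The same section therefore plans on incompatible ovulation rates for the same women.

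The effect size raises a second question. A 49-point difference is hard to square with a description of the observed effects as small.

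What is at stake is how the second factor's result is read. Someone told that 26 women suffice, in a trial of 240, could take a non-significant myo-inositol result as strong evidence of no added benefit. For modest gains it would be close to uninformative.

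**Working it through.** **1. Reproducing the plan's figure.** The inputs are 70% and 21%, 5% significance (taken as two-sided, since the article does not say) and 80% power. Using the unpooled formula for two proportions:

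n per group = (1.960 + 0.842)² × [p1(1−p1) + p2(1−p2)] / (p1−p2)²
= 7.849 × (0.2100 + 0.1659) / 0.2401 = 12.29, so 13 per group and **26 in total**.

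The same formula returns all three Table 1 totals:

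| Table 1 row | n per group | Total | Stated |
|---|---|---|---|
| 62% v 38% | 64.2 → 65 | 130 | 130 |
| 86% v 67% | 74.2 → 75 | 150 | 150 |
| 70% v 50% | 90.3 → 91 | 182 | 182 |

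The method is therefore identified, and the 26 is not a slip of calculation.

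**2. The placebo rate this design implies.** With 1:1 allocation at both stages, the placebo women are half letrozole and half GLC:

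- lowest row: (62 + 38)/2 = 50%
- median row: (70 + 50)/2 = 60%
- highest row: (86 + 67)/2 = 76.5%

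**3. Numbers per myo-inositol level.** 240 enrolled gives 120 per level. The plan's 182 evaluable gives 91 per level if losses are balanced.

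**4. Power against those rates.** Two-sided 5%, no interaction, with pooled variance under the null to match the planned chi-square test. With p̄ = (p1+p2)/2:

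z = [|p2−p1|√n − 1.960√(2p̄(1−p̄))] / √[p1(1−p1) + p2(1−p2)], and power = Φ(z).

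Example, 60% to 70% with n = 91: p̄ = 0.65, z = (0.954 − 1.322)/0.671 = −0.55, power 29%.

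The article gives no numerical effect on top of GLC or letrozole, so the gains below are assumed and shown as a range.

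| Placebo rate | Assumed gain | Power, 91 per level | Power, 120 per level | Total N for 80% |
|---|---|---|---|---|
| 50% | 10 points | 27% | 34% | 776 |
| 60% | 5 points | 10% | 12% | 2942 |
| 60% | 10 points | 29% | 37% | 712 |
| 60% | 15 points | 58% | 70% | 304 |
| 60% | 20 points | 84% | 93% | 164 |
| 76.5% | 10 points | 41% | 51% | 472 |

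**5. Smallest gain with 80% power.**

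| Placebo rate | 91 per level | 120 per level |
|---|---|---|
| 50% | 20.3 points | 17.8 points |
| 60% | 19.0 points | 16.8 points |
| 76.5% | 15.2 points | 13.5 points |

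The cited 70% on myo-inositol is itself only 10 points above the median-row placebo rate of 60%.

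**The case against.** The strongest reply is that the cited effect need not carry over as a fixed number of points. A reader might argue that 60% + 49 = 109%, so the assumption is impossible. That holds only on the risk-difference scale, and the article names no scale for its independent effects. On the odds scale, 70% against 21% is an odds ratio of (0.70/0.30)/(0.21/0.79) = 8.8. Applied to placebo rates of 50%, 60% and 76.5%, it gives about 90%, 93% and 97%. With 91 per level, power is then at least 98% in every case. This stands: if an effect that large held, the trial would detect it. It does not rescue the 26, which still assumes a 21% control rate.

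Second, a reader might infer that the article flatly contradicts itself on effect size. The remark under Statistical methods is unquantified, names no endpoint, concerns myo-inositol alone and is offered in support of assuming no interaction. It is in tension with 49 points but does not set an effect size.

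Third, a reader might pair the second trial's 65% with 21% and say the total should be larger than 26. The article gives no control rate for that trial and never makes that pairing, so this is not an error in the text.

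Fourth, GLC versus letrozole is the declared primary comparison, and a factorial trial need not be fully powered for its second factor. This is right. It limits the weight of the point, but it does not justify a printed claim of ample coverage.

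**Conclusion.** The point holds as a fault in the inputs, not in the arithmetic. The figure of 26 does not apply to this design, because Table 1 implies a placebo rate of 50–76.5%, not 21%. At 60%, 80% power requires a gain of about 19 points (91 per level) or 17 points (120 per level). Gains of 5 to 10 points have 10–37% power there.

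This rests on Table 1's literature rates, 1:1 allocation with balanced losses, no interaction and a two-sided test. A 21% placebo rate is not impossible in principle; it is incompatible with the article's own planning rates.

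Two stronger readings are not supported. One is that the trial cannot detect a myo-inositol effect: gains of roughly 20 points or more have about 79% power or better with 91 per level at placebo rates of 50–60%. The other is that the trial is too small overall: the 240 comes from the GLC versus letrozole comparison, which this point leaves untouched. Nor does the article say that a non-significant result would be reported as no benefit; that is a risk in how the coverage claim may be read.

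**What to change.** In the sample size section, delete the calculation giving 26 and the claim that it is covered. Replace it with a statement along these lines:

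- All participants receive GLC or letrozole, so the expected ovulation rate on placebo is about 60% (50–76.5% over Table 1).
- Assuming no interaction and a two-sided 5% test, the trial has 80% power for a myo-inositol gain of about 17–19 points at a 60% placebo rate (120 and 91 per level), or about 20 points at 50% with 91 per level.
- Smaller effects are not adequately powered, and the comparison will be reported as an estimate with a 95% confidence interval.

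The remark on small observed effects under Statistical methods should be reconciled with this text.

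The cost is a change of wording and a less favourable claim for the second factor. It needs no extra participants and no change to the randomization or the primary comparison. The article states that recruitment has not begun, so the change can be made before any data exist.
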